### Participant baseline characteristics

Table 1 presents the sociodemographic and baseline characteristics of patients enrolled in the study, both overall and by condition. The similarity of participants in the two conditions indicates the success of the random assignment. About three-fourths of the participants were men. The average age was in the mid-thirties, although participants were well-distributed across the age ranges. The sample was ethnically diverse, with one-third being Latino. The great majority of patients were enrolled and received the intervention while admitted to hospital emergency departments (versus those hospitalized in level 1 trauma centers). Severity of drug use varied, with over half of the sample screening “at risk” for drug use, and about 45% at “high” or “severe” risk [10,31]. Marijuana was by far the most commonly used drug (84%) followed by amphetamines (19%). Use of more than one substance (including alcohol) was common, with about half of the participants reporting such use patterns. A measure of self-efficacy for avoiding drugs [32] was “moderate” at baseline (3.2 on a five-point scale ranging from low to high self-efficacy). Acculturation level among the 232 Latino participants [33] was 3.6 on a five-point scale ranging from low acculturation to high acculturation. Although interview instruments and intervention materials were available in Spanish, it was rare for participants to ask to be interviewed in Spanish.

**Table 1 T1:** Characteristics of life shift/shift gears participants

	**Percent or mean (SD)**		
	**Overall**	**Life shift**	**Shift gears**
	**(N = 700)**	**(n = 346)**	**(n = 354)**
Gender (%)			
Male	75.4	76.2	74.6
Female	24.6	23.8	25.4
Age category (%)			
18-20	9.3	10.7	7.9
21-24	13.2	13.6	12.7
25-34	27.1	29.6	24.6
35-44	17.5	16.6	18.4
45-54	22.1	19.5	24.6
55+	10.9	10.1	11.6
Mean age in years	36.9 (13.2)	35.9 (13.3)	37.9 (13.0)
Race/ethnicity (%)			
Hispanic/Latino	33.1	32.5	33.7
African American	37.0	36.5	37.4
White	24.8	26.0	23.6
Other	5.2	5.0	5.3
Patient location (%)			
Emergency Department	83.5	84.3	82.6
Hospitalized for Trauma	16.5	15.7	17.4
DAST drug risk category (%)^a^			
At risk (scores 1–2)	55.1	55.0	55.2
High risk (scores 3–8)	41.1	40.6	41.7
Severe risk (scores 9–10)	3.8	4.4	3.2
Type of drugs used in the past 30 days (%)^b^			
Marijuana	84.4	87.5	81.4
Amphetamines	19.3	17.4	21.2
Cocaine	8.8	7.8	9.7
Heroin	7.8	6.1	9.6
Other opiates	7.4	7.6	7.3
Use of more than 1 substance, including alcohol (%)	49.9	47.9	51.9
Use of more than 1 substance, excluding alcohol (%)	30.4	29.6	31.3
Drug avoidance self-efficacy score (mean)^c^	3.2 (1.2)	3.2 (1.2)	3.3 (1.2)
Acculturation score among Latinos (mean)^d^	3.6 (1.2)	3.6 (1.3)	3.6 (1.2)

^a^ There was no “No risk” category due to the eligibility criterion.

^b^ Prevalence based on ASI-Lite individual drug use items.

^c^ Scores potentially ranged from 1 (low self efficacy) to 5 (high self efficacy).

^d^ Scores potentially ranged from 1 (low acculturated) to 5 (high acculturated).

### Process measurements

Activities of HEs were monitored on an ongoing basis through a variety of process measurements. Daily and weekly reports were designed and used to track the success of participant recruitment efforts. A Daily Recruitment Report (DRR) was submitted via email to project management and included total number of patients screened, number eligible for enrollment, total number enrolled, and reasons that otherwise eligible patients did not complete the enrollment process (e.g., interview interrupted, did not consent). The DRR provided a real-time picture of HE activity and allowed project management to give immediate positive feedback when an HE had a high enrollment day.

A Weekly Participant Recruitment Report (WPRR) was submitted by each HE at the same time each week that contained a greater level of detail about their recruitment efforts and the progress they were making toward overall recruitment goals. The information collected was tallied on a form throughout the week and then compiled into a report and disseminated to all project staff so everyone was apprised of recruitment status on an ongoing basis. The WPRR included the following variables: total patients screened, patients who refused initial screening, eligible participants who dropped out during the assessment, eligible participants who dropped out during the intervention, interrupted/incomplete enrollments, eligible participants who did not consent, eligible participants who did not have contact information, and completed enrollment interviews.

Collection of these process measures allowed project management to evaluate the implementation of the experimental design and make modifications as soon as shortcomings were identified, or if HE productivity began to wane (although it rarely did). For example, having this information in real time from the first day of participant recruitment resulted in immediate adjustments to HE work schedules to ensure recruitment activities were conducted on the days and times that they were most likely to yield results. Since the process measures were shared with the whole team, the information helped to motivate the HEs to engage in friendly competition with their colleagues and keep their individual recruitment numbers high. These measures also helped project management more accurately predict when recruitment goals would be attained, and plan accordingly.

Other process measures were collected as part of the participant interview process and recorded in the data collection instrument. Such variables included the hospital location and whether the participant was an emergency or trauma patient. This knowledge helped illuminate which locations and departments were the most fruitful for recruitment and which environments were best suited for administering SBI. Start time and end times of each intervention were also recorded, which served a dual purpose. First, it identified peak recruitment times, which was helpful for scheduling purposes. Second, it allowed project management to monitor the time HEs spent delivering the intervention. From a quality assurance perspective, it was critical to monitor the time of the brief interventions to ensure they were lasting the intended amount of time and that both the experimental and control groups received interventions of the same average duration.

Quality assurance was the responsibility of the project manager, who possessed a Master of Social Work with a concentration in administration, undergraduate education and experience in chemical dependency counseling, and multiple years of experience as a project manager. Drawing on this background, the project manager shadowed the HEs as they conducted participant enrollment interviews and, utilizing the observational checklist, was able to reinforce effective techniques and offer immediate feedback about areas in need of improvement. While the HEs’ performance generally met or exceeded expectations, there were rare instances in which the project manager observed drift from the experimental design. Most commonly, this occurred when a HE missed an opportunity to delve further into a participant’s behaviors and uncover motivation to change.

To mitigate the natural process of drift from the experimental design, the HEs remained engaged in ongoing training activities for the duration of the recruitment period. They met with the project manager on a regular basis and continued to engage in didactic and experiential MI training. They were also treated as a valuable project resource; when areas in need of improvement were identified, the HEs were actively solicited for feedback and suggestions on what could be done differently. By approaching the HEs in this collaborative manner, the project benefited from their insights while simultaneously strengthening their engagement in their respective roles.

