**Methods/design:**

A randomized two-group repeated measures design is being used in which drug-related outcomes of an intervention group will be compared with those of an attention-placebo control group. Selection of bicultural paraprofessional HEs—their training in research concepts, comorbid mental health issues, special treatment of marijuana use, and nonscripted enhanced motivational interviewing as well as their ongoing monitoring and evaluation—are among the features described. The HEs enrolled, consented, and conducted an intervention among 700 illicit drug users in two large hospital emergency departments/trauma units. To be eligible, a participant needed to be an adult (age ≥18 years), an English or Spanish speaker, awake and able to give consent, and reachable by telephone to schedule a six-month follow-up interview.

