
If an individual screened eligible and consented, he or she was then randomly assigned to one of two conditions. The intervention group (Life Shift) received SBI drug intervention matched to their DAST risk level and drug of choice as identified by participant self-report. To assess the “true” effect of the SBI intervention (i.e., minus the effects of attention), a control group received the same quantity of intervention in the area of driving and traffic safety (Shift Gears) that did not focus on drugged driving. Baseline and six-month follow-up measures were collected for all participants and included standardized subjective drug use measures from the Addiction Severity Index-Lite (ASI-Lite) [11] and other measures presumed to be targeted by the intervention (e.g., functional status, self-efficacy). At face-to-face follow-up conducted by separate measurement technicians, a hair sample in a length corresponding to past-month exposure was tested for the presence or absence of four major categories of illicit drugs (i.e., amphetamines and other psycho-stimulants, cocaine and its metabolites, opiates, and cannabinoids) to increase the accuracy of subjective abstinence reports. In addition, driving and traffic-safety control items were collected to test the result of the experimental manipulation, with the attention-placebo control group expected to have greater pre/post change on these measures than the SBI intervention group.

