#### Evaluation and credentialing

Upon completion of the training modules, the HEs were evaluated on their mastery of each content area. Written tests were administered, and each HE was observed while conducting mock interviews in both English and Spanish. Performance was scored using a highly customized observational checklist that included each task the HE was required to complete, from the initial greeting of a participant through screening, consent, assessment, and intervention. After successful completion of the tests and mock interviews, the HEs began participant recruitment.

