### Participant recruitment and follow-up

Participant recruitment was conducted from April 2010 through June 2011, with a total of 700 subjects enrolled. Modifications to the experimental protocol were minimal. Figure 1 presents a CONSORT diagram of the flow of patients through the trial. Over 18,000 patients were approached and screened for their eligibility and interest in participating. The great majority of those excluded did not meet the eligibility criteria (e.g., their alcohol use risk exceeded their drug use risk). Of those who were eligible to participate, 29% were excluded, with 9.5% refusing and 19.5% excluded for other reasons (e.g., being interrupted for a medical procedure, becoming too sick or too sleepy to continue). The six-month follow-up rate was 43% with no difference in reasons for loss by condition.

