### Outcome measures and analyses

Mixed model analysis of variance (ANOVA) procedures within a general linear model framework will be conducted on the key self-reported outcomes measured by the ASI-Lite. The ASI-Lite composite scores of recent drug use and related medical problems, psychiatric problems, and alcohol use will be analyzed along with health-care utilization outcomes to assess differential change by condition. Because of potential bias introduced by a less-than-ideal response rate, two sets of analyses for the self-reported data will be conducted: complete-case analyses of 294 participants with longitudinal data and intention-to-treat analyses using multiple-imputation data to deal with loss to follow-up (N = 700). With multiple imputation, missing follow-up values are replaced by a series of plausible values rather than by a single value [27-30]. For each outcome, we will use multiple imputation with a chained equation approach to create five imputed data sets and pool these results. Imputed outcome values will be predicted from baseline drug and alcohol use variables, gender, age, income, and drug avoidance self-efficacy. In addition to changes in composite scores, the ASI-Lite drug use scores will be dichotomized into a past 30-day drug use abstinence variable (yes/no) measured at the six-month follow-up. Results of hair analysis will be used to verify abstinence reports. When hair analysis is positive for drug use and self-report is negative for drug use, the participant will be considered nonabstinent.

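### The N = 700 set called intention-to-treat appears to leave out patients who were randomised but left during the session; the article gives no count of them

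*Protocol article*

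**What the plan says.** All references are to the protocol article.

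- **Time of assignment** (Design and procedures): "If an individual screened eligible and consented, he or she was then randomly assigned to one of two conditions". The two conditions then receive different sessions, one on drug use and one on driving and traffic safety.
- **Order of the health educator's tasks** (Evaluation and credentialing): the observational checklist runs "from the initial greeting of a participant through screening, consent, assessment, and intervention".
- **Weekly report** (Process measurements): the variables include "eligible participants who dropped out during the intervention, interrupted/incomplete enrollments, eligible participants who did not consent". Completed enrolment interviews are a separate item at the end of the same list.
- **Daily report** (same section): it records "reasons that otherwise eligible patients did not complete the enrollment process (e.g., interview interrupted, did not consent".
- **Exclusions among the eligible** (Participant recruitment and follow-up): "Of those who were eligible to participate, 29% were excluded, with 9.5% refusing and 19.5% excluded for other reasons". The examples of other reasons are "being interrupted for a medical procedure, becoming too sick or too sleepy to continue".
- **Who the 700 are** (Abstract, Methods/design): "The HEs enrolled, consented, and conducted an intervention among 700 illicit drug users". Participant baseline characteristics likewise speaks of patients as enrolled and given the intervention.
- **Analysis set** (Outcome measures and analyses): alongside a complete-case analysis of 294, the plan has "intention-to-treat analyses using multiple-imputation data to deal with loss to follow-up (N = 700").

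**The concern.** An intention-to-treat set holds everyone assigned to a condition. If people who left the session after assignment are missing from the file, the set has been selected after randomisation on an event that can depend on the arm, because the two sessions differ in topic. The comparison is then no longer fully protected by randomisation.

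Multiple imputation does not repair this. As described, it fills in six-month outcomes for people in the file who were lost to follow-up, and it cannot represent people who were never entered.

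The label matters more than usual here. With a six-month follow-up rate of 43%, the N = 700 analysis is the main counterweight to the complete-case analysis, and readers will rely on it being what it is called.

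**Working it through.** **Step 1. Were session drop-outs already randomised?** Assignment follows eligibility and consent, and the session follows assignment. Anyone who left during the intervention had therefore been randomised. This follows directly from Design and procedures.

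**Step 2. Are they inside or outside the completed enrolments?** The weekly report lists leaving during the intervention and completing the enrolment interview as separate items. Process measurements also says that the project manager shadowed enrolment interviews using the observational checklist, and Evaluation and credentialing says that this checklist extends through the intervention. The drift seen in those interviews concerned exploring motivation to change, which is session content. A completed enrolment interview therefore most naturally means one in which the session was finished.

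**Step 3. Are the 700 the completed enrolments?** The abstract and the baseline section describe the 700 as people who received the intervention. Nowhere does the text report any of the 700 as assigned but not treated, although the weekly report has a category for that event.

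**Step 4. Reproduce the article's figures.**

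- Arms in Table 1: 346 + 354 = 700.
- Exclusions: 9.5% + 19.5% = 29.0%.

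**Step 5. Implied counts**, assuming that the 700 are the eligible patients who were not excluded.

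- Eligible = 700 / (1 − 0.29) = 985.9, about 986.
- Refused = 0.095 × 985.9 = 93.7, about 94.
- Other reasons = 0.195 × 985.9 = 192.3, about 192.
- Rounding of the 29% matters little: 28.5% to 29.5% gives 979 to 993 eligible and 191 to 194 excluded for other reasons.

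**Step 6. Possible size.** Let s be the share of the 192.3 who left after assignment. The article does not give s, so the full range is shown. Number left out k = s × 192.3; randomised = 700 + k; share left out = k / (700 + k); share with complete data = 294 / (700 + k).

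| s | Left out (k) | Randomised | Share left out | Complete cases as share of randomised |
|---|---|---|---|---|
| 0% | 0 | 700 | 0% | 42.0% |
| 10% | 19 | 719 | 2.7% | 40.9% |
| 25% | 48 | 748 | 6.4% | 39.3% |
| 50% | 96 | 796 | 12.1% | 36.9% |
| 100% | 192 | 892 | 21.5% | 33.0% |

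The last row is an upper bound, since it needs every interruption to fall after assignment.

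**Step 7. Do the arm sizes show anything?** An exact binomial test of 346 out of 700 against an assumed 1:1 allocation gives p = 0.79. Unequal loss between arms leaves no visible trace in the totals. Near-equal totals cannot exclude a difference in the kind of patient who left.

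**The case against.** The strongest reply is that no sentence says a randomised patient was removed from the 700. The weekly report is a recruitment-monitoring form, not a definition of an analysis set. Its items are neither strictly exclusive, since the list opens with everyone screened, nor in time order, since non-consent comes after leaving the session. A person tallied as leaving mid-session could still be in the file, and with sessions of 10 to 30 minutes the number could be zero or very small. The only direct statement about the analysis set calls it intention-to-treat. The CONSORT figure, which might show the counts, is missing from the text at hand, and that is no fault of the plan.

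Most of this stands. It rules out any statement that exclusion after randomisation has been established, and it means that 0% belongs in the range. It does not remove the point: the description of the enrolment interview and of the 700 favours the reading that session drop-outs are outside the set, and nothing in the text says that they are inside.

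Three stronger readings are tempting and not supported:

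- **That the 19.5% were randomised patients.** Interruption, sickness or sleepiness could have occurred at consent or assessment. The daily report pairs interruption with non-consent as a failure to complete enrolment, and the weekly report lists interrupted enrolments separately from leaving during the intervention.
- **That patients left the drug session more often than the driving session.** No counts by arm are given, the sessions were designed to the same duration, and patients could equally leave a talk on driving.
- **That the health educators' reservations about the control session drove selective loss.** Module 1 does record the reservations. It also says that they came to endorse the design, with quality monitoring cited in support, and candidates with such conflicts were screened out at hiring.

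**Conclusion.** The concern holds in a limited form. Patients who left during the session had been randomised, and the article's account of the enrolment interview and of the 700 most naturally places them outside the set that it labels intention-to-treat. This is an inference from several sections read together and not a rule that the article states.

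The size cannot be fixed from the document: 0 to about 192 people, or 0% to an upper bound of about 21.5% of those randomised. Many interruptions probably preceded assignment, so the true figure may lie well below that bound. The range assumes that the 700 are the 71% of eligible patients not excluded, and that session drop-outs, if left out, sit within the category of other reasons. The direction of any bias is unknown.

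It still calls for action rather than a note, because the article itself fixes N = 700 as intention-to-treat, and because the abstract says that outcome analysis is not complete, so the set or its label can still be corrected.

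**What to change.** 1. Reconcile the assignment record with the list of 700, using the weekly reports to identify anyone who left or was interrupted after assignment.
2. Define the intention-to-treat set as everyone assigned to a condition, whether or not the session was finished.
3. Include any session drop-outs, with the baseline data they gave, in the multiple imputation. Because the checklist places assessment before the intervention, those who left mid-session should have at least some baseline data.
4. Report the number randomised and the number who left during the session, by arm, in the text and the CONSORT flow.
5. If these records cannot be recovered, call the N = 700 analysis *randomised and completed the session* instead of intention-to-treat, and give the exclusions by arm.
6. If the reconciliation finds that all 700 are everyone assigned, one sentence saying so closes the point.

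The cost is some reconciliation of existing records and a somewhat larger imputed share. On the complete-case count of 294, that share is now 1 − 294/700 = 58.0%. It would be 59.1% if 10% of the other exclusions came after assignment, and 67.0% at the upper bound.

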## Discussion

### Strengths

Training personnel to conduct SBI as part of standard medical care requires a comprehensive approach, but training paraprofessional HEs to conduct those same services for a randomized controlled trial requires greater depth and breadth of training. Although Life Shift/Shift Gears had not been completed at the time of publication, the study’s carefully monitored implementation and subsequent recruitment of 700 participants is a testament to the strength of the training curriculum. As observed through a variety of process and quality assurance measures, HEs consistently delivered quality SBI services to participants while adhering to the experimental design.

The customized curriculum allowed the HEs to develop a true appreciation for the experimental design, strong MI skills, and enhanced critical thinking skills about the complex issues of drug use and behavioral change. The extensive role-playing, followed by the evaluation and credentialing process, bolstered HE preparedness to begin participant recruitment. Once recruitment began, monitoring their activities allowed for modifications to the schedule and associated protocol and safeguarded against drift from the experimental design. Regular training kept HE skills current so they were able to deliver high-quality services throughout the duration of the recruitment period. Finally, by treating the HEs as valued, integral members of the team, they were encouraged to contribute at higher levels while concurrently strengthening their dedication to the project.

